Pre-exposure prophylaxis (PrEP) is highly effective in preventing HIV transmission and remains the centerpiece of HIV prevention efforts in the United States, yet the scale-up of PrEP has led to stark disparities by race and ethnicity, limiting its impact [3]. PrEP is well tolerated, available in inexpensive generic forms, and prevents over 99% of HIV transmission when taken as directed. In numerous areas, including the United States [4] and New South Wales [5], scale-up of PrEP has been associated with reductions in new HIV transmission at the population level. Despite the spectacular promise of PrEP, less than half of persons in the United States indicated for PrEP were taking it in 2024 [6]. From 2012 to 2017, PrEP use increased by an average of 56% annually [7], followed by a more gradual annual growth of 18% from 2018 to 2021 [3]. The PrEP-to-need ratio (PnR) is a measure of PrEP use that compares the number of PrEP users in a group or geographic area (numerator) to the number of HIV diagnoses (denominator) [8]. This metric has been used to measure PrEP uptake among groups that would most benefit from it in numerous studies and has been used in other areas such as the US Centers for Disease Control and Prevention’s (CDC) recent examination of mpox vaccine provision [9]. PnR assessments have revealed lower PrEP use among Black and Latinx persons, younger persons, women, and persons in the US South relative to epidemic burden [3,10]. Additionally, modeling suggests that the greatest overall HIV epidemic reduction occurs in scenarios with equal PrEP provision relative to HIV burden across racial groups (PnR=1) [11]. Thus, increasing uptake of PrEP in areas with greatest need, as defined by higher HIV incidence, maximizes the number of new infections averted for a given level of PrEP use. National disparities in PrEP provision by race, however, have increased over time [12]. There is an urgent need to identify policies and programs that improve PrEP uptake and PnR.

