Despite substantial scale-up of PrEP attributable to past efforts and policies, legal and program environments in which PrEP-eligible people live are highly heterogeneous, and evidence regarding policy impact is lacking. The United States has made significant efforts to scale up HIV PrEP through EHE Programs, with over US $1.5 billion invested in HIV prevention from 2020 to 2024 [13]. EHE funding has been granted to the EHE priority jurisdictions through the Health Resources and Services Administration and CDC mechanisms that allowed state and local health departments and community health centers to implement HIV prevention and treatment initiatives. Diverse programs have been implemented with this funding—ranging from social media messaging to medical records improvements, and from clinician training to telemedicine PrEP prescribing [14-16]—yet, no research program has sought to determine the comparative effectiveness and efficiency of these PrEP interventions on a population basis to guide future investments. Outside of HIV EHE efforts, PrEP uptake may also be influenced by state-level policy decisions and the availability of CDC grant programs such as grants that were designed to support PrEP demonstration projects. Both Medicaid expansion and the use of Pre-Exposure Prophylaxis Drug Assistance Programs (PrEP DAP) offer promising approaches that are associated with increased PrEP use that is also more aligned with epidemic need [17]. It is critical to identify the program elements that have contributed most to successful outcomes within each PrEP service.

National prescription, medical, and diagnosis datasets using data from commercial entities are robust and capture a majority of all US prescriptions with line-level, deidentified individual data [17]. These comprehensive datasets enable accurate, nationwide data on PrEP prescribing, which can be used to develop valuable insights on HIV prevention efforts when analyzed in tandem with data regarding PrEP policies and programs provision. Moreover, such aggregated datasets allow for data to be rapidly assessed regarding the uptake of newer PrEP formulations and modalities (eg, long-acting injectable [LAI] PrEP medications), providing information regarding the use and care characteristics of newer PrEP modalities relative to previously approved modalities.

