**Primary outcomes**							
	PrEP starts	New PrEP users in each jurisdiction per time period		National PrEP database		PrEP initiation/population	
	PrEP start needs	New PrEP users, ratio-to-need in jurisdiction per time period		National PrEP database		PrEP initiation/HIV diagnoses	
	PrEP retention	User retained in care per time period		National PrEP database		Average retention time/population	

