#### Primary Outcome Measures

When possible, we will use PrEP outcomes that have been previously defined in prior literature [7,8,17,24-30]. Given a range of analyses across objectives 1-3 that include exploratory, quasi-experimental, and modeling that will require different time horizons and levels of aggregation, we anticipate a number of different PrEP outcomes across analyses for this research program. When appropriate, we will assess PrEP use in terms of starts and retention. PrEP starts will be defined as the number of persons starting PrEP per 100,000 population (PrEP starts per capita). For monthly assessments of this outcome, a PrEP start is defined as a person initiating PrEP for the first time or reinitiating PrEP after a lapse in prescription of a cut point, such as at least 1 month, calculated from the biweekly proportion of days covered (PDC) reaching 0.57 or lower (eg, less than 4 days per week). PDC measures the percentage of days that filled medication prescriptions could provide coverage for a period if the medication is taken as prescribed. The PDC metric has been commonly used in PrEP studies [24,25,27,28,31] and has been suggested as a good metric for studies focusing on PrEP use at specific time points [24]. We will conduct sensitivity analyses to assess the impact of different cut points for lapses in coverage. For retention in care, all PrEP fills not classified as PrEP starts will be considered prescriptions obtained while retained in PrEP care. PrEP retention will be defined as consecutive PrEP prescription refills based on their PrEP modalities, calculated as the time period in continuous PrEP care. For analyses that aggregate beyond the monthly level, such as yearly analyses, we will use definitions previously used in the literature and by the CDC. For yearly analyses, this involves counting any people with a prescribed day of PrEP in that calendar year, including persons with sufficient pills prescribed in the prior year to have days prescribed in the following year [3,8]. We will also analyze how PrEP is used relative to need by assessing the number of persons using PrEP per new HIV diagnosis (PnR). For models in objective 3, the primary outcomes will be HIV infections averted and cost-effectiveness.

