To understand the impact of PrEP policies and programs (objective 2), we will leverage the legal coding and health jurisdiction program provision datasets described above to conduct quasi-experiments with outcomes of PrEP starts, PnR, and retention in care. PrEP programs have been adopted by local health authorities in the context of the disbursement of EHE funds as grants to applicants. Despite the lack of random assignment of jurisdictions to policies and programs, we propose a quasi-experimental design that allows us to have findings that reflect several of the characteristics of randomized studies, including temporality and controlling for time-invariant factors. Although quasi-experimental approaches are subject to some limitations inherent to nonrandomized designs such as challenges in controlling for time-varying characteristics, these designs minimize bias relative to other analysis approaches. Moreover, quasi-experimental approaches improve upon the external validity of randomized studies because the data stem from programs that have been enacted in practice. Because of the study design, results will be well positioned to inform real-world programs such as those that comprise EHE efforts. For quasi-experiments, we will conduct analyses using methods such as difference-in-differences (DID) that account for intervention and control jurisdiction trends before program implementation. Because interventions are implemented at different points in time, we will use the heterogeneous DID method proposed by Callaway and Sant’Anna [32] or a similar method to account for potential confounding from multiple implementation periods. Health jurisdictions implementing a program or policy will be the primary intervention unit, and controls will be jurisdictions not implementing a program. DID analyses will be accomplished with regressions that include a term for group (eg, telemedicine PrEP program or not), period (month), and group-by-period interactions that serve to estimate the effect of the intervention. Our approach provides a relatively large sample size for such analyses, with many of the 50 counties or local jurisdictions funded under the EHE program implementing programs under assessment, and other non-EHE jurisdictions also implementing some of the identified programs. Control jurisdictions will be counties or states in the United States that do not implement a particular program, using 9 years of monthly PrEP use data (2016-2024). Depending on characteristics of the intervention, such as statewide provision, we may restrict the control group to jurisdictions meeting certain criteria in order to improve the match between intervention and control groups. For instance, we might match counties by HIV prevalence or jurisdiction size.

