
Although we have conducted substantial outreach to health jurisdictions to optimize engagement, we anticipate that there will be some missing data from the health jurisdiction survey. It is likely not a valid approach to impute data on whether a program was implemented in a particular jurisdiction. Therefore, analyses will be conducted only among jurisdictions providing data. To explore the impact of the missingness, we will assess descriptive differences between missing and nonmissing jurisdictions for the outcome over time and for key sociodemographic variables. Our outcome assessment will include the determination of policy impacts on PnR, an equity metric. Additionally, we will identify potential inequities in PrEP use based on key geographic, socioeconomic, and demographic characteristics. This may be conducted empirically with interaction terms between the policies of interest and these characteristics. DID models assume that trends in the intervention and control groups are parallel before the intervention. This is a critical consideration because control jurisdictions might have additional interventions to the one under consideration. We will seek to assess the validity of this premise, using techniques such as visual assessments of event-study plots and the Granger causality test to determine whether the design is sufficient to meet the parallel trends assumption. If parallel trends assumptions are not met, we will consider alternative approaches such as multivariable matching, lagged dependent variable regression, and synthetic control models (adapted for multiple treated units). The synthetic control method uses a matching algorithm to create a weighted dataset for the control (nonintervention) group, assigning a weight to each element in the group to eliminate prior differences in critical covariates and the outcome. Another option is to use difference-in-difference-in-differences (DDD) to assess the additional change from a specific policy (eg, telemedicine) above and beyond the overall EHE program effect for funded EHE jurisdictions. The nature of the DID and DDD designs controls for confounders that do not vary over time. Therefore, to optimize model efficiency, we will not control for variables expected to remain constant over time (eg, area-level poverty), only adding time-variant covariates. To further ascertain the validity of the DID approach, we will conduct placebo tests for policies that our models have found to have statistically significant effects on PrEP use. These tests assign earlier implementation dates selected at random (eg, false) to treated units to observe if we continue to reject the null hypothesis under these “false” implementation dates. Statistically insignificant results from the placebo tests will increase confidence that the model outcomes are valid. Further, we will assess the sensitivity of our models to the implementation time period by conducting the Bacon-Goodman [33] decomposition and reporting any disproportionate influence of certain implementation periods. We will seek to conduct additional sensitivity analyses that explore whether funding levels determine the impact of programs, with the program intervention variable being related to prevention budget expended rather than whether the program was enacted. Analyses will be conducted in SAS 9.4, STATA 19, or similar software. Given that there are multiple policies, it will be critical to address challenges with multiple comparisons. To accomplish this, we will, where possible, seek unified model approaches that simultaneously test the effects of multiple programs.

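### A difference-in-differences effect on PnR in objective 2 mixes a change in PrEP use with a change in HIV diagnoses, because the denominator can itself move after the program starts

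*Protocol article*

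**What the plan says.** - The Data Analyses section plans, for objective 2, to "conduct quasi-experiments with outcomes of PrEP starts, PnR, and retention in care". It then adds: "Our outcome assessment will include the determination of policy impacts on PnR, an equity metric".
- Background says that PnR "compares the number of PrEP users in a group or geographic area (numerator) to the number of HIV diagnoses (denominator". Primary Outcome Measures describes it as "assessing the number of persons using PrEP per new HIV diagnosis (PnR".
- Table 1 lists a companion outcome, starts-to-need, as "New PrEP users, ratio-to-need in jurisdiction per time period", with the formula "PrEP initiation/HIV diagnoses".
- On what might move the denominator, Background reports that "scale-up of PrEP has been associated with reductions in new HIV transmission at the population level". It also says EHE funding "allowed state and local health departments and community health centers to implement HIV prevention and treatment initiatives".
- No section sets the denominator at a pre-program value, lags it, or treats diagnoses as an outcome in objective 2. The Limitations section does not raise the matter.
- PrEP starts per 100,000 population and retention in care are analysed in parallel. Neither has a diagnosis denominator.

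**The concern.** Difference-in-differences (DID) attributes to the program whatever changes in the outcome differ between intervention and control jurisdictions after the start date. When the outcome is a ratio, that includes changes in the denominator. By the article's own reasoning, new diagnoses lie downstream of PrEP and of other funded HIV work, so the denominator is a post-program quantity.

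Three consequences follow, and they differ in kind:

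- If a program raises PrEP use and diagnoses fall because of it, the PnR effect has the right sign but is larger than the PrEP effect.
- If diagnoses fall more in intervention jurisdictions for a reason other than PrEP, PnR rises with no change in PrEP use.
- If diagnoses rose more in intervention jurisdictions, a real PrEP gain would be reduced or cancelled in PnR.

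The stake is what a PnR effect can support. Objective 2 is meant to identify programs that improve PrEP provision relative to need, and objective 3 takes effectiveness estimates from the DID analyses into a transmission model. The article does not say which outcome supplies those estimates. If it were a PnR effect, a fall in transmission already contained in the input could be generated again by the model.

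**Working it through.** **Is there a figure in the plan to reproduce?** Not for PnR. The only objective 2 figure is the detectable difference of 2.4 PrEP starts per 100,000 at 90% power. With the stated inputs (6 and 238 counties, 300 users each, 60 months, SD 73, correlation 0.05, significance 0.05 taken as two-sided), the slope-difference formula gives

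3.2415 × 73 × √(1/1,800 + 1/71,400) × √(12 × 0.95 × 59 / (60 × 61)) = 2.42,

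which agrees. It concerns starts only and says nothing about PnR.

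**Decomposition.** Let *p* be the relative change in PrEP users, and *d* the relative change in new diagnoses, each for intervention relative to control jurisdictions from before to after the program. Then

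PnR ratio = (1 + *p*) / (1 + *d*).

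With the denominator fixed at its pre-program value, the ratio is simply 1 + *p*. The same identity holds for starts-to-need, with starts in place of users.

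**Illustration.** The article gives no value for *d*, and the values of *p* and *d* below are assumptions chosen to show a range.

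| PrEP change *p* | Diagnosis change *d* | Same-period PnR | Fixed-denominator PnR |
|---|---|---|---|
| 0% | −5% | 1/0.95 = 1.053, +5.3% | 0% |
| 0% | −10% | 1/0.90 = 1.111, +11.1% | 0% |
| 0% | −20% | 1/0.80 = 1.250, +25.0% | 0% |
| +10% | −10% | 1.10/0.90 = 1.222, +22.2% | +10% |
| +10% | +5% | 1.10/1.05 = 1.048, +4.8% | +10% |
| +10% | +10% | 1.10/1.10 = 1.000, 0.0% | +10% |
| +10% | +20% | 1.10/1.20 = 0.917, −8.3% | +10% |

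**Would the planned checks find it?**

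- The parallel-trends assessment (event-study plots, Granger test) judges the period before the program. A denominator shift that starts with the program leaves that period untouched.
- Placebo tests move the start to an earlier, false date, so they too look at the time before the shift.
- The decomposition by implementation period concerns the influence of timing groups, not the two parts of the ratio.
- The triple-difference design is offered as an option. It could subtract a shift common to EHE-funded areas, but not one specific to the program or one caused by PrEP itself.
- The COVID-19 sensitivity analyses address the pandemic, not diagnosis changes that come with a program.

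**The case against.** The other side has several good points.

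- **Same-period timing is inferred.** Table 1 speaks of a time period, while Background and Primary Outcome Measures give no timing. The outcomes section defers where possible to published definitions, and a fuller plan might settle it. This stands as a caveat. Even so, the article defines the outcome without any lag or baseline, and same-period is the natural reading.
- **The shift is not confined to treated jurisdictions.** A reader might infer that co-funded treatment work falls only on the intervention side. The article does not support that: exposure is defined program by program, an EHE-funded area without a given program can be a control, and non-EHE areas run some of the programs. The point needs a differential shift, not an exclusive one.
- **A rise in diagnoses has no stated basis.** A reader might infer that the programs expand case finding. No passage says that a PrEP program raises diagnoses, so the masking direction is conditional.
- **A PrEP-driven fall in diagnoses does not flatter an ineffective program.** A program that does not raise PrEP use causes no such fall. A false gain needs a route other than PrEP.
- **No gain is lost to the study as a whole.** Starts per capita and retention would still show it. The plan also describes PnR as efficiency, use relative to need, and equity, rather than as plain uptake. This limits the harm, but PnR remains a named causal outcome, and per-capita starts do not measure use relative to need.
- **Replacing the denominator outright would cost something.** A fixed denominator turns PnR into a rescaled PrEP count and drops current need. With data updates to 2028, a 2016–2018 denominator could be ten years old. This is why the fixed version should be added and not substituted.

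**Conclusion.** The point holds in a limited form. As defined, a DID effect on PnR is the PrEP effect divided by the diagnosis effect, and the article gives reasons of its own to expect the second to differ from one. A PnR effect on its own therefore does not show that a program raised PrEP relative to need. Across the assumed range, falls of 5% to 20% in diagnoses produce PnR gains of 5.3% to 25.0% with no change in PrEP, and a 10% fall turns a 10% PrEP gain into 22.2%.

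This rests on three assumptions: that the denominator is contemporaneous, that diagnoses change differently in intervention and control jurisdictions, and that the sizes shown are only illustrative. The documents do not establish how large any real shift would be. Nor do they support concluding that PnR is unusable or that objective 2 as a whole would miss a real PrEP gain. It is a matter of what is reported beside PnR and what is claimed from it.

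**What to change.** Keep same-period PnR as the descriptive measure of use relative to need. For every DID or triple-difference analysis of PnR and of starts-to-need:

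1. Report beside it, separately, the estimated effects on PrEP users (or starts) and on new HIV diagnoses.
2. Add a version whose denominator is each jurisdiction's pre-program diagnoses, using one calendar window for treated and control units within an analysis, since controls have no start date of their own. For EHE-era programs, 2016–2018 would serve, because the study period begins in 2016 and EHE launched in 2019. Policies that began before 2019 need an earlier or lagged window. A lag protects only while it still reaches back before the start.
3. State in advance that a program will be called effective at raising PrEP relative to need only where the fixed-denominator or the numerator effect supports it.

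The cost is some plan wording, one more derived variable and one more set of models. For EHE-era programs the 2016–2018 window lies inside the study period; an earlier window would need diagnosis counts from before it. The fixed version will not reflect later changes in need, which is why the same-period series stays in the report.

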**PrEP user and structural covariates**							
	Age (years)	18-24, 25-39, 40-54, 55 or older^c^		National PrEP database		Age of individual PrEP user	
	Race and ethnicity	Black, Latino or Hispanic, White, Asian, other^c^		National PrEP database		Race and ethnicity of individual PrEP user	
	Gender	Male and female^c^		National PrEP database		Self-identified gender of PrEP user	
	Copay	Average PrEP copay in dollars		National PrEP database		Copay of individual PrEP user	
	PrEP payer	Commercial, government, and other		National PrEP database		Insurer or payer of the PrEP prescription	
	Provider	National Provider Identifier		National PrEP database		Unique identification number of providers	
	Jurisdiction characteristics	% Bachelor’s degree holder, % living in poverty, % uninsured, % Black residents, % Latinx residents		US Census		Proportion of county residents with a characteristic	

^a^Summary of PREMISE research program constructs, including primary explanatory variables, primary outcomes, program covariates, and PrEP user and structural covariates, with corresponding levels or definitions. The table also lists data sources and how each variable is defined for analysis.

^b^PrEP: pre-exposure prophylaxis.

^c^Line-level data acquired from health exchanges. Granular data are not always available such as other identity and additional racial or age categories.

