**External clinical programs**			
	Safety-Net PrEP Clinic	Delivery of PrEP through an existing STI^d^ clinic, community health center, pharmacy, or similar public health clinic, aimed at expanding PrEP access among key populations through reduced cost or free services	
	Telemedicine PrEP	Consists of full or hybrid telemedicine PrEP services that reduce or eliminate the need for in-person clinical visits	
	PrEP Assistance Program	Cover the cost of PrEP-related services, either directly or indirectly, usually by reimbursing providers for clinical visits and lab tests, or paying PrEP-related out-of-pocket costs to health plans	
	PrEP navigation services	Provide assistance to find a PrEP provider and address barriers to access PrEP, as well as support strategies to facilitate retention or reinitiation into PrEP care	

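### The objective 2 covariate rule leaves out fixed jurisdiction traits on the ground that DID controls them, but DID removes only their constant effect on level and not a trend linked to them; the rule also does not exclude covariates that a program can change.

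*Protocol article*

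**What the plan says.** The Data Analyses section of the protocol article gives the reasoning: "The nature of the DID and DDD designs controls for confounders that do not vary over time". From this it concludes, for the sake of model efficiency, that "we will not control for variables expected to remain constant over time (eg, area-level poverty), only adding time-variant covariates". It does not name the time-variant covariates and sets no condition that a program must not affect them.

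The estimator is set in the same section: "Because interventions are implemented at different points in time, we will use the heterogeneous DID method proposed by Callaway" and Sant'Anna, or something similar. The section also describes a regression with group, month and group-by-month terms.

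Table 1 lists the covariates for the whole research program. Among them are "Average PrEP copay in dollars", payer, and a row of census characteristics that includes "living in poverty, % uninsured, % Black residents, % Latinx residents". Table 1 does not say which of these enter the objective 2 models. Table 2 includes a PrEP assistance program that works by covering visits and tests "or paying PrEP-related out-of-pocket costs to health plans". Table 3 adds PrEP DAP and Medicaid expansion to the policies under study.

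The trend safeguards are event-study plots and a Granger test, followed by a fallback: "If parallel trends assumptions are not met, we will consider alternative approaches such as multivariable matching", lagged dependent variable regression or synthetic control. Matching controls on HIV prevalence or size is mentioned as something that might be done. Placebo dates are planned for effects found to be statistically significant.

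**The concern.** A fixed trait drops out of a DID contrast only if its effect on the outcome is the same before and after the program. If counties with that trait were already growing faster or slower in PrEP starts, or began to do so after adoption, the difference in growth is credited to the program. This is the main form of confounding left in a DID design.

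The protocol gives reason to take this seriously. Its Background says "National disparities in PrEP provision by race, however, have increased over time", so composition may predict growth as well as level. EHE counties were chosen for HIV burden, and programs came through grants to applicants, so adopters may differ from non-adopters on the same traits. The named estimator can condition parallel trends on pre-program covariates, and the rule gives up that option.

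The second part is what the rule lets in. Copay, payer mix and % uninsured can be moved by PrEP assistance, PrEP DAP and Medicaid expansion. Adjusting for their post-program values would remove the share of the effect that runs through them.

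Objective 2 estimates feed the objective 3 infection and cost-effectiveness models, so a bias here would carry forward.

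**Working it through.** **1. The benchmark.** The power section states 90% power for a difference of 2.4 starts per 100,000. Its inputs are 6 and 238 counties, 300 persons per county, 60 months, SD 73, within-person correlation 0.05 and alpha 0.05 (taken as two-sided). For a time-by-treatment slope test with compound symmetry, the detectable divergence over the period is

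(z₀.₉₇₅ + z₀.₉₀) × SD × √[(1 − ρ)/Σ(t − t̄)²] × √(1/n₁ + 1/n₀) × (T − 1)

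with n₁ = 6 × 300 = 1,800, n₀ = 238 × 300 = 71,400 and Σ(t − t̄)² = 60 × (60² − 1)/12 = 17,995:

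3.2415 × 73 × √(0.95/17,995) × √(1/1,800 + 1/71,400) × 59 = **2.42**.

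This reproduces the stated 2.4. It serves only as a yardstick here: it is a divergence accumulated over a 60-month follow-up, not an average DID effect.

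**2. Bias from a trend linked to a fixed trait.** Let g be the treated-control gap in monthly growth of the start rate that goes with the trait. The documents give no value for g. Assume growth differs by 0.05 to 0.1 starts per 100,000 per month per SD of the trait, and that treated counties differ by 0.5 SD. Then g = 0.5 × 0.05 = 0.025 to 0.5 × 0.1 = 0.05.

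The panel for 2016-2024 is 9 × 12 = 108 months. For a mid-panel start (also assumed) there are 54 months on each side.

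- Pooled pre/post contrast: midpoints are 54 months apart, so bias = 54g.
- Last pre-program month as base: mean distance is (1 + 54)/2 = 27.5 months, so bias = 27.5g.

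| g per month | Last-pre-period base | Pooled pre/post |
|---|---|---|
| 0.025 | 0.69 | 1.35 |
| 0.05 | 1.38 | 2.70 |

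The bias can have either sign. A gap of 2.4/54 = 0.044 (pooled) or 2.4/27.5 = 0.087 (last-pre-period base) would by itself produce an apparent effect of 2.4.

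**3. Simulation of the trend problem.** Illustrative settings: 6 treated and 238 control counties, 60 months with a start at month 30, true effect 2.4, residual SD 5, trait gap 1 SD, 400 replicates. Expected bias is 1 × drift × 30.

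| Drift per month | Expected bias | DID without trait | DID with trait predicting change |
|---|---|---|---|
| 0 | 0 | 2.39 | 2.39 |
| 0.02 | 0.6 | 2.98 | 2.37 |
| 0.04 | 1.2 | 3.58 | 2.39 |
| 0.08 | 2.4 | 4.78 | 2.40 |

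With no drift the protocol's reasoning is right. With drift it is not.

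**4. Simulation of a covariate changed by the program.** Same layout, using the conventional two-way regression, with a covariate that carries part of the effect.

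| Share of effect carried | Not adjusted | Adjusted |
|---|---|---|
| 0% | 2.41 | 2.44 |
| 25% | 2.41 | 1.82 |
| 50% | 2.32 | 1.19 |
| 75% | 2.43 | 0.62 |

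Adjustment removes roughly the share that the covariate carries. The shares are assumptions.

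**The case against.** A reader might infer that differential trends go wholly uncontrolled. The documents do not support that. The protocol plans event-study plots and a Granger test, and it names matching, lagged dependent variable regression and synthetic control if parallel trends fail. A steady linear drift like that in the working would also run through the pre-program months, where these checks look. This stands, and the accurate claim is that such trends are addressed only if detected or if an optional step is taken. Matching is something that might be done, and the alternatives are to be considered. Detection may be hard with as few as 6 treated counties, and a pre-trend check cannot see divergence that begins after adoption. EHE investment from 2020 overlapped the pandemic, which the Limitations section says affected PrEP use. Placebo dates are tied to significant results, so a bias that hides a real effect would escape them.

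A reader might also infer that the plan will adjust for copay, payer or % uninsured in the insurance and cost analyses. No section says so. Table 1 serves all objectives, and % uninsured shares a row with poverty, the protocol's example of an excluded variable. With pre-program covariates in the named estimator, post-program copay would not be adjusted for; the danger comes with the conventional regression, which the section also describes. Choosing particular covariates can be left to an analysis plan. What remains is that the stated rule uses variation over time as its criterion and does not exclude covariates affected by a program.

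Finally, the widening racial disparity is national. It does not show that county composition predicts growth in starts, or that adopting counties differ in composition. The trend confounding is plausible, not demonstrated.

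**Conclusion.** The inference behind the covariate rule is wrong, and the rule should be changed. DID does not remove a trend associated with a fixed trait, so the main objective 2 model makes no adjustment for baseline traits that may predict both adoption and PrEP growth. The safeguards are real but partial.

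The size cannot be fixed from the documents. Under the assumed growth gap of 0.025 to 0.05 per month and a mid-panel start, the bias is about 0.7 to 1.4 starts per 100,000 with a last-pre-period base and 1.35 to 2.7 with a pooled pre/post contrast. A reader might conclude that the bias exceeds the stated 2.4. That happens only at the upper assumed gap with the pooled contrast, not with a last-pre-period base for the named estimator, and the 2.4 rests on 60 months where this illustration uses 108. The supportable statement is that modest growth gaps could produce a bias that is a sizeable fraction of the effect the study is designed to detect.

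Over-adjustment for program-affected covariates is a risk that the rule permits. It is not a stated plan.

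**What to change.** Replace the rule in Data Analyses with three statements:

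- A short, prespecified set of jurisdiction covariates may predict trends, for example two or three of poverty, race and ethnicity composition, HIV prevalence and population. Measure them before each unit's own program start. Implement this as conditional parallel trends in the Callaway-Sant'Anna estimator, or as baseline-by-period terms in a regression.
- Post-program values of covariates that a program can affect (copay, payer mix, % uninsured) are not adjusted for in objective 2 models.
- The unadjusted estimate is reported alongside.

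The cost is mainly wording. Poverty, composition and population are available from census data, and the protocol already contemplates matching on HIV prevalence and size. The downside is some loss of precision or overlap when few counties are treated. With a minimum of 6, divided further by adoption date, a doubly robust fit on a long covariate list would not be workable, which is why the set should be short. A single calendar baseline for all programs should be avoided, since it would not be pre-program for any unit that adopted earlier.
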